### Other Study Parameters

At baseline, we will also gather data on demographics and comorbidities. We will also perform a general physical examination. The demographic dataset will include age, sex, ethnicity, marital status, work status, education, smoking status, and alcohol consumption, as well as disease duration, autoantibody status, and presence of erosions. Furthermore, we will ask for the presence of the following comorbidities: diabetes, inflammatory bowel disease, cardiovascular diseases, urinary tract disorders, and malignancies. During the general physical examination, we will measure the height, weight, and waist circumference. Height and weight will be used to calculate the BMI.

### Sample Size

The HELIA is a superiority trial, powered to detect a 20% difference in DAS28 and DAPSA remission and/or successful tapering of DMARD treatment after 12 months of follow-up. Meeting either criterion is sufficient to qualify for the primary outcome. Murray et al [55] showed that after the first year of diagnosis, remission rates are up to 30%. Although tapering of treatment is still not standard of care, previous research has shown that tapering of treatment in patients with LDA is possible [56]. Based on these data, we assumed that 30% of the patients in the control group, general nutrition recommendations, will reach remission or be able to successfully taper their medication and that this will be 20% higher in patients who will follow the online, interactive lifestyle intervention program. Thus, to detect this 20% difference using a significance level of *α*=.05 (2-sided) and a power of 80%, 100 patients per group (~75 RA and ~25 PsA) are needed, also taking a 10% dropout ratio into account, which is based on previous trials conducted in the Erasmus MC [57,58].

### Statistical Analysis

#### Overview

Primary and secondary end points are analyzed according to an intention-to-treat principle, also known as full analyses. In an intention-to-treat analysis, all patients are analyzed in the groups to which they were randomized, regardless of whether they received or adhered to the allocated management approach.

Reporting of results will be in accordance with the CONSORT (Consolidated Standards of Reporting Trials) statement. Means (SD) will be presented for normally distributed data and medians (IQR) for nonnormally distributed data. Frequencies are presented as the number of patients (proportion).

We assume that missing data are (missing) at random. Therefore, missing data, in baseline variables as well as in the follow-up data, will be handled with multiple imputations by chained equations, with 40 imputations [59]. A Bonferroni correction will be applied if necessary to account for multiple testing by dividing the *P* value by the number of tests performed. All data analysis, including cleaning, transforming, and modeling, will be done in STATA18 (StataCorp LLC) or higher.

#### Primary End Point Analyses

The primary end point is the proportional difference in DAS28 and DAPSA remission and/or those who were able to taper their medication without having a disease flare after 12 months of follow-up between patients with IA who followed the lifestyle intervention program and those who received general nutrition recommendations [23,26]. Meeting either criterion is sufficient to qualify for the primary outcome. Logistic regression will be used to compare aforementioned differences at 12 months, in which intervention allocation, diagnosis (RA or PsA), biologic or targeted synthetic DMARD usage at randomization (yes or no), age (years), and sex are the covariates. If baseline imbalances in CRP, tender and swollen joint counts between both interventions occur, we will also correct for these imbalances.

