#### Inclusion Criteria

The inclusion criteria for this study are as follows:

1. Diagnosed with RA or PsA according to the American College of Rheumatology or European Alliance of Associations for Rheumatology (EULAR) 2010 criteria or Classification for Psoriatic Arthritis criteria, respectively [21,22].2. LDA, defined as DAS28 ≥2.6 and <3.5 or DAPSA >4 and <16 [23,24].3. Stable DMARD dosage and oral prednisone (or equivalent) at a dose ≤7.5 mg for ≥6 months prior to randomization.4. Age ≥18 years.

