### Primary End Point

The primary objective is the proportional difference in DAS28 and DAPSA remission and/or successful tapering of DMARD treatment after 12 months of follow-up. Meeting either criterion is sufficient to qualify for the primary outcome.

Disease activity in patients with RA and PsA is measured with the DAS28 and DAPSA, respectively [23,24]. The DAS28 is a pooled index that involves the incorporation of a 28-joint count for tenderness (TJC28), a 28-joint count for swelling (SJC28), an erythrocyte sedimentation rate (ESR) and GH (measured with a Visual Analog Scale [VAS] 0‐100 mm) into a formula to obtain a numerical indicator of disease activity. The DAS28 formula is 0.56√(TJC28)+0.28√(SJC28)+0.70ln(ESR)+0.014(GH) [23]. The DAPSA is also a pooled index, which is made up of the following five domains: (1) a 68-joint count for tenderness, (2) a 66-joint count for swelling, (3) a CRP (expressed in mg/dL), (4) a patient’s assessment of the disease activity (VAS, 0‐10 cm), and (5) a patient’s assessment of pain severity (VAS, 0‐10 cm). The numerical values of the aforementioned 5 domains are summed to provide the DAPSA score [24]. The threshold values for DAS28 and DAPSA remission are <2.6 and ≤4, respectively [24,26]. The minimal clinically important differences (MCIDs) for the change in DAS28 and DAPSA are 1.2 and 7.2, respectively [27,28]. Tapering of treatment is left to the discretion of the treating rheumatologist in consultation with the patient, with current treatment recommendations as a guideline.

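### The primary logistic model leaves out baseline DAS28/DAPSA and adjusts for CRP and joint counts only if an undefined baseline imbalance appears

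*Protocol article*

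**What the plan says.** Protocol article, Primary End Point Analyses, specifies a logistic regression for the 12-month outcome and lists its terms: "intervention allocation, diagnosis (RA or PsA), biologic or targeted synthetic DMARD usage at randomization (yes or no), age (years), and sex are the covariates". The baseline DAS28 or DAPSA is not among these terms. The next sentence reads: "If baseline imbalances in CRP, tender and swollen joint counts between both interventions occur, we will also correct for these imbalances". It names no test, threshold or form of adjustment.

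Inclusion Criteria sets the entry range: "LDA, defined as DAS28 ≥2.6 and <3.5 or DAPSA >4 and <16". Primary End Point sets the target: "The threshold values for DAS28 and DAPSA remission are <2.6 and ≤4, respectively". That section also builds DAS28 from 28-joint counts, ESR and general health, and DAPSA from 68/66-joint counts, CRP and two patient scales. Remission or successful tapering is enough for success.

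Randomization and Blinding balances allocation on diagnosis only and masks group labels during analysis. Sample Size gives "we assumed that 30% of the patients in the control group" and "this will be 20% higher in patients who will follow the online, interactive lifestyle intervention program", and concludes with "a power of 80%, 100 patients per group (~75 RA and ~25 PsA) are needed", dropout included.

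**The concern.** Every patient starts above a cut-off and succeeds on the remission component by falling below it. Distance from the cut-off at entry is therefore an obvious candidate covariate, yet neither the randomisation nor the model accounts for it.

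The conditional rule does not fill the gap, for three reasons.

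- **Wrong trigger.** A covariate earns its place by predicting the outcome. Chance imbalance in a randomised trial is not a reason to select it.
- **Wrong variables.** CRP is not part of the protocol's DAS28, and about three quarters of the patients have RA. Even when the rule is triggered, ESR and general health stay unadjusted in RA. Joint counts run to 28 in RA but to 68 and 66 in PsA, so a single pooled joint-count term mixes scales.
- **No definition.** Three optional covariates without a criterion allow up to 2³ = 8 primary models on the same data.

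At stake are some precision that could be had at almost no cost, and a primary result that two analysts could obtain from different models. Because the odds ratio is non-collapsible, adding a covariate also changes which odds ratio is estimated.

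**Working it through.** **1. The planned sample size.** Inputs from Sample Size: 30% versus 50%, two-sided α 0.05, power 80%, dropout 10%. With unpooled variance, n = (0.30×0.70 + 0.50×0.50) × (1.960 + 0.842)² / 0.20² = 0.46 × 7.85 / 0.04 ≈ 90.3, so 91 per arm, and 91/0.9 gives 102. The stated 100 per group is reproduced to within 3%. With 90 evaluable per arm (100 less 10%), power is 78.7%. The calculation uses no covariates.

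**2. How far the starting score could matter.** The protocol does not give the SD of 12-month change, so it is assumed. With no mean change, the chance of DAS28 <2.6 is Φ((2.6 − x)/SD) for entry at x. At x = 2.60 this is 50%. At x = 3.49 it depends on the SD:

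| Assumed SD of change | Chance of DAS28 <2.6 from 3.49 |
|---|---|
| 0.5 | 4% |
| 0.6 | 7% |
| 1.0 | 19% |
| 1.2 | 23% |

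These figures compare the two ends of the entry window and concern remission only.

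**3. Power with and without adjustment.** Simulated logistic regressions: 30% versus 50%, 90 per arm, 4,000 trials per scenario, simulation error about 0.6 points. The strength of the baseline score is assumed. The triggered rule is modelled generously, as adjustment for the baseline score itself when its imbalance has P<0.05.

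| Odds ratio per SD | Not adjusted | Triggered | Always adjusted |
|---|---|---|---|
| 1.5 | 78.6% | 78.6% | 79.9% |
| 2.0 | 79.2% | 79.2% | 82.1% |
| 2.5 | 77.7% | 78.5% | 84.3% |
| 3.0 | 79.6% | 80.2% | 86.9% |

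A second simulation used the eligibility windows directly (baseline uniform, 68 RA and 22 PsA per arm, remission only):

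| Assumed SD of change, DAS28 / DAPSA | Not adjusted | Triggered | Always adjusted |
|---|---|---|---|
| 1.2 / 8 | 78.8% | 78.8% | 80.0% |
| 1.0 / 7 | 80.0% | 80.1% | 81.5% |
| 0.7 / 5 | 78.8% | 79.7% | 83.4% |
| 0.5 / 4 | 79.7% | 80.4% | 85.7% |

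Across both, always adjusting gains about 1 to 7 points, and the triggered rule gains less than 1. The second table probably overstates the gain, since tapering gives a route to success that need not depend on the starting score.

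**4. Type I error.** Under 30% in both arms and an odds ratio per SD of 1.5 to 3.0, a mechanical P<0.05 trigger gave 3.8% to 4.9%. Taking either the adjusted or the unadjusted result, whichever is significant, gave 5.9% to 7.0%.

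**5. How often a trigger would fire.** If imbalance meant P<0.05 on any of three independent measures (an assumed criterion), chance alone would trigger it in 1 − 0.95³ = 14.3% of trials. Correlation between the measures lowers this, to about 13% at 0.4.

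**The case against.** The best case for the plan has four parts.

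- **Prognostic strength is not documented.** The DAS28 window is 0.9 wide, narrower than the protocol's own minimal clinically important difference of 1.2, and tapering alone can make a success. This stands. A reader might infer that the starting score is the strongest predictor of the endpoint, or that it largely fixes the result. The protocol does not support either, and the 4 to 7% figures need an SD of change as small as 0.5 to 0.6.
- **Power is as planned.** A reader might infer that the omission leaves the trial underpowered. It does not: the sample size takes no credit for covariates, so the omission only forgoes a gain, and a gain of about 1 point is close to simulation noise.
- **The rule is closed and the analyst is masked.** Only three variables are eligible, and a fixed trigger did not inflate type I error. Both are true, so the rule does not inflate error by its nature. But no trigger is fixed, and a two-sided P value is the same whichever arm carries which label, so masking does not prevent choosing a model by its result. An analysis plan not shown here could define the trigger, but it would still select covariates for the wrong reason.
- **The effect measure is another matter.** A reader might infer that the plan reports an odds ratio where a difference in proportions is wanted. The section names the model but not the reported measure, and logistic regression validly tests a difference between proportions. This supports an optional improvement, not an error.

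**Conclusion.** The point holds in a limited form. The primary model omits a baseline score that is expected to be prognostic for remission, and in its place has an undefined, data-dependent rule that uses poorly matched variables. The cost is a forgone gain of roughly 1 to 7 power points, probably towards the low end, under assumed prognostic strengths that the protocol does not give. The model-choice risk is a type I error of about 6 to 7% in the specific case of picking whichever result is significant. Nothing in the protocol suggests that this is intended. It should be corrected, but it does not undermine the design.

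**What to change.** Before unmasking, by a dated and justified amendment:

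1. Always include baseline disease activity in the primary model (DAS28 in RA, DAPSA in PsA, standardised within diagnosis), together with the five terms already listed.
2. Delete the sentence on imbalances in CRP and joint counts, or move it to a labelled sensitivity analysis.
3. Optionally, report from the same model the adjusted risk difference with 95% CI by marginal standardisation. This matches the 20-point difference on which the trial was sized. On that scale 30% versus 50% is 20 points; as an odds ratio it is (0.5/0.5)/(0.3/0.7) = 2.33.

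No new data are needed, because the scores are collected at baseline and missing baseline values are already to be imputed. The real cost is a documented late change to the primary model. The Results section says that the analysis plans have not changed since registration. Recruitment ended in May 2024, so the last 12-month visits fell due around May 2025. The amendment should therefore state its date and confirm that no outcome comparison by arm had been seen.

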#### Secondary End Points Analyses

The ICER will be used as an outcome for the cost-effectiveness analysis. The ICER is the ratio of the difference in total costs to incremental benefits (QALYs) between both management approaches. Total costs are divided into health care (direct) and productivity (indirect) costs, which will be analyzed from a societal perspective [31]. QALYs are calculated as the area under the curve of the EQ-5D-5L [30]. A probabilistic sensitivity analysis will be performed for the estimation of the ICER by bootstrapping with 1000 iterations using a Monte Carlo simulation. Results will be plotted in a cost-effectiveness plane, which will be used to estimate the 95% CI of the ICER. Additionally, a cost-acceptability curve will be extracted to show the probability of each intervention being cost-effective at different levels of willingness-to-pay thresholds in comparison with each other. Sensitivity analysis will be performed to assess the main drivers of cost-effectiveness.

Other secondary end points are health risk, weight, BMI and waist circumference, and PROs, including GH, pain, morning stiffness, fatigue, functional ability, and quality of life, at baseline, after 3 months, 6 months, 1 and 2 years of follow-up, and over time between both groups. A Student *t* test, chi-square test, or Wilcoxon rank-sum test will be used to compare the difference in aforementioned outcomes at fixed time points, when appropriate. Additionally, a mixed model with an unstructured covariance matrix will be used to compare outcomes over time. In all analyses, we will correct for our randomization minimization procedure. Moreover, the PRO difference will be weighed against the MCID.

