### Randomization and Blinding

Patients are randomized with a 1:1 allocation ratio into the intervention group (participating in the online, interactive lifestyle intervention program) or the control group (receiving general nutrition recommendations), using ALEA clinical software (ALEA Clinical B.V.). The allocation sequence was balanced for diagnosis (RA or PsA). Patients, treating physicians, RNs, and researchers will know to which group patients are randomized. The principal investigator will generate the allocation sequence and will assign participants to interventions using ALEA clinical software. RNs will enroll participants and do not have access to the randomization sequence. During statistical analysis, treatment allocation will remain concealed through the use of masked group labels.

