### Secondary End Points

Secondary end points include cost-effectiveness, health risk, and (self-reported) disease burden (refer to Table S1 in Multimedia Appendix 1). Cost-effectiveness will be evaluated through the ICER, which is the ratio of the difference in costs to incremental benefits between the online interactive lifestyle intervention program and general nutrition recommendations. For the cost-effectiveness analysis, we will calculate the quality-adjusted life years (QALYs) and total costs. QALYs express the impact of the disease on patients’ health over time. Living in perfect health corresponds to a QALY of 1 and a QALY of 0 reflects death [29]. QALYs are determined by calculating the area under the curve of the EQ-5D-5L [30]. Costs are divided into direct and indirect costs. We will analyze direct and indirect costs from a societal perspective. Direct costs are the costs of treatment and medical consumption, whereas indirect costs are costs due to loss of productivity [31]. Medication costs are calculated from doses reported in the patients’ case records, valued according to the Dutch National Health Care Institute [32]. Medical consumption, including duration of hospitalizations and admission diagnosis, are recorded every 3 months with the Institute for Medical Technology Assessment medical consumption questionnaire. We will use the Dutch average length of stay by diagnosis if the duration of hospitalization is unknown. Indirect costs include not fully functioning (presenteeism), sick leave (absenteeism), and reduction in work time [33]. Work Productivity and Activity Impairment (WPAI) outcomes are expressed as impairment percentages, with higher numbers indicating greater impairment and less productivity.

The health risk is assessed by measuring weight, BMI, and waist circumference. BMI is calculated by dividing the patient’s weight (kg) by the square of their height (m). A BMI ranging from 18.5 to <25 is classified as a healthy weight. A BMI between 25 and <30 is categorized as overweight, while a BMI ≥30 is considered obese. Conversely, a BMI <18.5 is classified as underweight [34]. Sex-specific thresholds for waist circumference are associated with an elevated risk of metabolic complications. In males, a waist circumference ≥94 cm is linked to an increased risk, whereas a measurement of ≥102 cm corresponds to a substantially increased risk. For females, these thresholds are ≥80 cm and ≥88 cm, respectively [34].

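### No covariate adjustment beyond, at most, diagnosis is stated for incremental costs, although b/tsDMARD use and baseline costs are available and should predict follow-up cost

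*Protocol article*

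**What the plan says.** The section Secondary End Points Analyses defines the ICER: "The ICER is the ratio of the difference in total costs to incremental benefits (QALYs) between both management approaches". On uncertainty it says: "A probabilistic sensitivity analysis will be performed for the estimation of the ICER by bootstrapping with 1000 iterations using a Monte Carlo simulation". A cost-effectiveness plane, an acceptability curve and a sensitivity analysis of the main drivers follow. No regression model and no covariate is named for costs.

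The next paragraph of that section, on the other secondary end points, contains a general statement: "In all analyses, we will correct for our randomization minimization procedure". The only factor named under Randomization and Blinding is diagnosis: "The allocation sequence was balanced for diagnosis (RA or PsA").

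The section Primary End Point Analyses does list covariates. Besides allocation and diagnosis, "biologic or targeted synthetic DMARD usage at randomization (yes or no), age (years), and sex are the covariates".

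Under Secondary End Points, drug cost is part of total cost: "Direct costs are the costs of treatment and medical consumption, whereas indirect costs are costs due to loss of productivity". Its source is also given: "Medication costs are calculated from doses reported in the patients’ case records, valued according to the Dutch National Health Care Institute".

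Table 2 ticks the medical consumption questionnaire (MCQ), the WPAI, the EQ-5D-5L and DMARD history at T0. Inclusion criterion 3 requires a stable DMARD dosage for at least 6 months before randomisation.

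**The concern.** The plan adjusts the clinical outcome for b/tsDMARD use at entry but names no such adjustment for costs, where the variable acts most directly. Patients enter on stable treatment, so entry use should largely carry into follow-up drug cost. Allocation was not balanced on it. If one arm has more users by chance, an unadjusted cost difference reflects that as well as any effect of the programme.

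Cost-effectiveness is the first-listed secondary objective, and the Discussion addresses the results to policymakers and insurers. Tapering is part of the primary end point, so lower drug spending is a plausible route to a cost effect. A saving of that kind is easier to read once the drug mix at entry is accounted for.

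**Working it through.** **1. What is fixed for each analysis**

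| Item | Primary end point | Incremental cost |
|---|---|---|
| Estimator | Logistic regression | Difference in total costs, bootstrapped |
| Diagnosis | Covariate | Only if the all-analyses sentence reaches the ICER |
| b/tsDMARD use at randomisation | Covariate | Not named |
| Baseline value of the outcome | Disease-activity components if imbalanced | Not named |

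Even on its widest reading, the all-analyses sentence adds diagnosis and nothing else.

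**2. The sample size used below**

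The only design figure is 100 per group (30% v 50%, two-sided alpha 0.05, power 80%, 10% dropout). With unpooled variance, n = (0.3×0.7 + 0.5×0.5)×(1.960 + 0.842)²/0.20² = 0.46×7.85/0.04 = 90.3, so 91. Then 91/0.9 = 101.1, so 102, within two of the stated 100. The pooled formula gives 93, then 104. No figure is stated for costs, so there is none to reproduce. I use 100 per arm.

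**3. Chance imbalance in b/tsDMARD use**

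The documents do not give the share of users p, so it is assumed. The SD of the arm difference is √(2p(1−p)/100).

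| Assumed p | SD (points) | 95% range (points) | Probability of a gap of 10 points or more |
|---|---|---|---|
| 0.2 | 5.7 | ±11.1 | 7.7% |
| 0.3 | 6.5 | ±12.7 | 12.3% |
| 0.4 | 6.9 | ±13.6 | 14.9% |

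**4. What a gap would do to an unadjusted cost difference**

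Shift = gap × extra annual drug cost per user. The documents give no price. For a 10-point gap:

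- assumed EUR 3,000: 0.10×3,000 = EUR 300 per patient-year
- assumed EUR 6,000: EUR 600
- assumed EUR 12,000: EUR 1,200

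This takes entry use as carrying fully into follow-up; tapering or switching would reduce it.

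**5. Precision**

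Let rho be the correlation between the baseline covariates, taken together, and follow-up total cost. It is assumed. Adjustment multiplies the variance of the cost difference by about 1 − rho².

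- rho = 0.3: variance falls by 9%; interval width × √0.91 = 0.954, about 5% narrower; equivalent to 100/0.91 = 110 per arm.
- rho = 0.5: variance falls by 25%; interval width × √0.75 = 0.866, about 13% narrower; equivalent to 100/0.75 = 133 per arm.

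**6. Are the covariates available?**

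MCQ and WPAI at T0 give baseline medical consumption and productivity loss. b/tsDMARD use at randomisation is already needed for the primary model. Baseline drug cost is not a T0 item in Table 2, but it can be derived, because "Medication costs are calculated from doses reported in the patients’ case records". EQ-5D-5L at T0 supplies the baseline utility for a QALY model.

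**The case against.** The strongest reply is that the ICER sentence is a definition and holds whether or not the two differences are adjusted. The article never calls the cost difference raw. A condensed article may leave the health-economic model to a document not shown. This stands in part: a reader might infer that the sponsor has decided on an unadjusted comparison, and the text does not support that. But the article sets out the economic analysis in some detail and lists covariates where it has chosen them. The one correction it does state cannot supply b/tsDMARD use or baseline costs.

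The second reply is about harm. An unadjusted randomised difference is unbiased. The bootstrap resamples patients together with their costs, so the plane and acceptability curve already carry the sampling variation in drug use. This stands in full. A reader might take the euro shifts above as a hidden error on top of the reported interval, or as a biased ICER. They are neither; they are one component of the uncertainty that the interval already shows.

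Third, prices, user share and rho are all assumed, and total cost also includes hospital stays and productivity loss, which may swamp drug cost. The trial is not powered for costs, so a power gain on a cost test has no planned analysis to attach to. This stands, and it limits the claim to a conditional statement about precision.

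Fourth, adjusting costs but not QALYs would put estimates with different covariates on the same plane. This is correct, so the remedy has to cover both.

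**Conclusion.** The point holds as one of efficiency and prespecification, not of validity. For incremental costs the article states no adjustment beyond, at most, diagnosis, and it is unclear whether even that reaches the ICER. b/tsDMARD use at randomisation and baseline costs are not named, although the first is in the primary model, was not balanced at allocation and should predict follow-up drug cost.

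The consequence is lost precision and a possible shift in the single realised estimate. The documents do not allow its size to be calculated. For an assumed rho of 0.3 to 0.5, cost variance would fall by 9% to 25%; at the lower end the gain is small. For an assumed 20% to 40% users, a gap of 10 points or more between arms has a probability of about 8% to 15%. The change is worth making because it costs little and because this is an open-label trial: adjustment fixed in advance cannot be seen as a response to an observed imbalance.

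**What to change.** Before the analysis that follows the last visit (May 2026):

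1. State whether the correction promised for all analyses covers the ICER, and with which factors.
2. Within each bootstrap replicate, estimate incremental costs by regression of total cost on allocation, diagnosis, b/tsDMARD use at randomisation and baseline costs (T0 MCQ and WPAI, with baseline drug cost derived from case records).
3. In the same replicate, estimate incremental QALYs with a matching adjusted model that includes baseline EQ-5D-5L.
4. Take the adjusted pair to the plane and the acceptability curve, and report the unadjusted result as a sensitivity analysis.

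The cost is a few lines of analysis-plan wording and code, plus the derivation of baseline drug cost from records already used for costing. The small downside is that a regression form for skewed costs must be chosen and prespecified, since that choice can move the estimate. Whatever form is chosen, it should return a difference in mean costs, because that is what the ICER uses.

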**Figure 2. F2:**
[figure not shown]
Participant timeline.

**Table 2. T2:** Overview of data collection in intervention and control groups.

Data collection	T0	T3	T6	T12	T24
In-hospital evaluation					
Diagnosis: RA^a^ or PsA^b^	✓				
Check other inclusion and exclusion criteria	✓				
Informed consent	✓				
Demographic	✓				
History (fulfillment ACR^c^/and EULAR^d^ criteria for RA and PsA, disease duration, auto-antibody status, presence of erosions, DMARD^e^ history)	✓				
Comorbidity	✓				
Global assessment of disease activity by patient and RN^f^	✓	✓	✓	✓	✓
Adverse events (self-reported)		✓	✓	✓	✓
Hospital admission		✓	✓	✓	✓
Length, Weight, BMI, and waist circumference	✓	✓	✓	✓	✓
Physical examination by RN	✓	✓	✓	✓	✓
Online questionnaires					
General (smoking, alcohol, and drugs)	✓				
General health (VAS^g^)	✓	✓	✓	✓	✓
Pain (VAS)	✓	✓	✓	✓	✓
Morning stiffness (severity and duration; NRS^h^)	✓	✓	✓	✓	✓
Fatigue (VAS and FACIT-F^i^)	✓	✓	✓	✓	✓
HAQ^j^ (functional ability)	✓	✓	✓	✓	✓
EQ-5D-5L (quality of life)	✓	✓	✓	✓	✓
SF-36^k^ (quality of life)	✓			✓	✓
RAPID-3^l^	✓	✓	✓	✓	✓
Sleep (MOS-SS^m^)	✓	✓	✓	✓	✓
Perceived stress	✓	✓	✓	✓	✓
Physical activity	✓	✓	✓	✓	✓
Diet compliance	✓	✓	✓	✓	✓
WPAI^n^ (work and productivity)	✓	✓	✓	✓	✓
Medical consumption (MCQ^o^)	✓	✓	✓	✓	✓
Total time (min)	~34	~30	~30	~34	~34
Routine laboratory tests	✓	✓	✓	✓	✓

a RA: rheumatoid arthritis.

b PsA: psoriatic arthritis.

c ACR: American College of Rheumatology.

d EULAR: European Alliance of Associations for Rheumatology.

e DMARD: disease-modifying antirheumatic drug.

f RN: research nurse.

g VAS: Visual Analog Scale.

h NRS: Numeric Rating Scale.

i FACIT-F: Functional Assessment of Chronic Illness Therapy-Fatigue.

j HAQ: Health Assessment Questionnaire.

k SF-36: 36-item Short Form Health Survey.

l RAPID-3: Routine Assessment of Patient Index Data 3.

m MOS-SS: Medical Outcomes Study sleep scale.

n WPAI: Work Productivity and Activity Impairment.

o MCQ: Medical Consumption Questionnaire.

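### No adjustment for baseline EQ-5D-5L is planned for the incremental QALY, which costs precision and lets chance baseline differences shift the ICER denominator

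*Protocol article*

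**What the plan says.** The protocol article defines the QALY twice in nearly the same terms. Under Secondary End Points: "QALYs are determined by calculating the area under the curve of the EQ-5D-5L". Under Secondary End Points Analyses: "QALYs are calculated as the area under the curve of the EQ-5D-5L". The latter section then sets the estimand and the handling of uncertainty: "The ICER is the ratio of the difference in total costs to incremental benefits (QALYs) between both management approaches", and "A probabilistic sensitivity analysis will be performed for the estimation of the ICER by bootstrapping with 1000 iterations using a Monte Carlo simulation".

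One sentence there deals with adjustment: "In all analyses, we will correct for our randomization minimization procedure". Randomization and Blinding names one balancing factor: "The allocation sequence was balanced for diagnosis (RA or PsA"). The tests and the mixed model described in the same section are for the other secondary endpoints, not for the QALY.

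Baseline adjustment is treated more fully for the primary endpoint. Primary End Point Analyses lists the model terms: "intervention allocation, diagnosis (RA or PsA), biologic or targeted synthetic DMARD usage at randomization (yes or no), age (years), and sex are the covariates". It adds a conditional correction if CRP or joint counts differ between groups at baseline. Baseline EQ-5D-5L appears in neither list. Table 2 schedules the EQ-5D-5L at T0, T3, T6, T12 and T24 in both groups.

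**The concern.** A participant's baseline utility is part of his or her area under the curve and is normally correlated with every later value. If the QALY contrast is adjusted for diagnosis alone, a utility difference present by chance at randomisation is counted with the effect of the programme, and the between-patient variation that baseline utility explains stays in the error.

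This matters for a ratio. The QALY difference is the ICER denominator and may well be small, so modest movements in it can shift the ratio, the cost-effectiveness plane and the acceptability curve. Cost-effectiveness is the first-listed secondary objective, and the Discussion hopes that the results will persuade policymakers and insurers to reimburse lifestyle programmes.

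**Working it through.** **Plan figure.** The article gives no figure for the QALY or ICER analysis. The group size used below, 100, comes from Sample Size and is about right for the primary endpoint: with 30% v 50%, two-sided 0.05 and 80% power, (1.96 + 0.842)² × (0.21 + 0.25)/0.20² gives 91 per group, and 91/0.9 gives 102. Nothing below changes it.

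**Inputs from the article.** Visits at 0, 3, 6, 12 and 24 months (Participant Timeline); 100 per group; EQ-5D-5L MCID 0.04 (Secondary End Points).

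**Assumptions, not in the article.** EQ-5D-5L SD 0.20 (range 0.15 to 0.25); the same correlation ρ between any two visits, 0.3 to 0.7. The cost-effectiveness text does not tie the QALY to one horizon, so both are shown.

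**Step 1: trapezoid weights in years.**
- 12 months: 0.125, 0.25, 0.375, 0.25 (sum 1).
- 24 months: 0.125, 0.25, 0.375, 0.75, 0.50 (sum 2).

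The baseline value's own weight is 0.125/1 = 12.5% of a 12-month QALY and 0.125/2 = 6.25% of a 24-month QALY.

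**Step 2: slope of QALY on baseline utility.** With T the horizon in years, slope = 0.125 + ρ(T − 0.125).
- 12 months: 0.125 + 0.875ρ.
- 24 months: 0.125 + 1.875ρ.

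**Step 3: one-SE baseline gap.** SE = 0.20 × √(2/100) = 0.028. A gap at least this large, in either direction, occurs by chance in about one trial in three. The expected shift in the QALY difference is slope × 0.028.

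**Step 4: precision.** In units of SD², the QALY variance is V = (1 − ρ)Σw² + ρT², with Σw² = 0.28125 (12 months) or 1.03125 (24 months). Then R² = slope²/V, and adjustment multiplies the SE by √(1 − R²). At 12 months and ρ = 0.5: V = 0.1406 + 0.5 = 0.6406, R² = 0.5625²/0.6406 = 0.494, and √0.506 = 0.71.

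| Horizon | ρ | Slope | Shift from one-SE gap | SE unadjusted → adjusted | SE ratio |
|---|---|---|---|---|---|
| 12 months | 0.3 | 0.39 | 0.011 | 0.020 → 0.017 | 0.84 |
| 12 months | 0.5 | 0.56 | 0.016 | 0.023 → 0.016 | 0.71 |
| 12 months | 0.7 | 0.74 | 0.021 | 0.025 → 0.014 | 0.55 |
| 24 months | 0.3 | 0.69 | 0.019 | 0.039 → 0.034 | 0.87 |
| 24 months | 0.5 | 1.06 | 0.030 | 0.045 → 0.033 | 0.74 |
| 24 months | 0.7 | 1.44 | 0.041 | 0.050 → 0.029 | 0.58 |

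**Step 5: benchmark in QALYs.** The MCID of 0.04 is a utility difference. Sustained, it is worth 0.04 QALY over one year and 0.08 over two. The shifts are therefore 0.011/0.04 = 27% to 0.021/0.04 = 52% at 12 months, and 0.019/0.08 = 24% to 0.041/0.08 = 51% at 24 months.

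**Step 6: where the shift comes from.** The baseline value's own contribution is 0.125 × 0.028 = 0.0035 QALY. The rest arises because baseline predicts later utilities.

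**Sensitivity to SD.** For SD 0.15 to 0.25 the one-SE gap is 0.021 to 0.035. Across ρ 0.3 to 0.7 the shift is then 0.008 to 0.026 over 12 months and 0.015 to 0.051 over 24 months. The SE ratios do not depend on the SD.

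**The case against.** The strongest objection is that the sentences cited define each patient's QALY, not how the groups are compared. An area under the curve is also the right outcome for a baseline-adjusted regression. A reader might infer that the plan fixes a raw, wholly unadjusted comparison, but the text does not say so, and its sentence on correcting for the randomisation procedure points to at least some adjustment. A health-economic or statistical analysis plan not shown may name further covariates. This stands as a limit on the claim. It does not remove the point: the article does state an adjustment for these analyses, and anyone following it would adjust for diagnosis and leave baseline utility out.

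Second, chance imbalance is ordinary sampling variation. Randomisation removes bias on average, and a bootstrap that resamples patients already carries this variation into the plane and the acceptability curve. That is correct. A reader might infer a biased ICER; the design does not support that. What remains is avoidable width and a shift conditional on the imbalance that this trial happens to have.

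Third, the size rests on an SD and a correlation that the article does not give. Entry is restricted to low disease activity on stable treatment, which could weaken the correlation. This also stands, and is why the range goes down to ρ = 0.3, where the gain in SE is only 13 to 16%.

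**Conclusion.** The point holds as an improvement available at no cost, not as an error that invalidates the analysis. As written, the incremental QALY is adjusted at most for diagnosis, although a strong predictor is measured at T0. Under the stated assumptions, a one-SE chance gap moves the QALY difference by about a quarter to a half of a sustained 0.04 utility difference, and adjustment reduces the SE by 16 to 45% at 12 months and 13 to 42% at 24 months. The direction holds for any positive correlation; the size depends on the assumed correlation and, for the shift, on the SD.

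Two stronger readings should be avoided. Setting the 24-month shift of 0.041 against 0.04 would make it look as large as the whole MCID, but the two-year counterpart is 0.08 QALY. Nor can one say that the cost-effectiveness conclusion would change: the article gives no expected QALY difference, no costs and no willingness-to-pay value, and an MCID is not an expected effect.

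**What to change.** Add one sentence to Secondary End Points Analyses, or to the analysis plan: the incremental QALY is the allocation coefficient from a linear regression of QALY on allocation, baseline EQ-5D-5L and diagnosis, refitted in each of the 1000 bootstrap samples, and the ICER, the plane and the acceptability curve are built from these adjusted estimates. If an analysis plan not shown already says this, a reference to it is enough.

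The change needs no new data and leaves the sample size and the QALY definition as they are. The last visit is planned for May 2026 and analysis follows it, so the wording can be dated and fixed before analysis begins.
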